## Abstract

**Introduction:**

Individual, social and economic circumstances faced by young mothers (19 years or under) can challenge a successful start in life for their children. Intervening early might enhance life chances for both mother and child. The Family Nurse Partnership (FNP) is an intensive nurse-led home visiting programme developed in the US which aims to improve prenatal health behaviours, birth outcomes, child development and health outcomes, and maternal life course. Establishing evidence of effectiveness beyond the original US setting is important to understand where further adaptation is required within a country specific context.

**Objective:**

This study will form one strand of the Scottish Government’s plan to evaluate the effectiveness of FNP as compared to usual care for mothers and their children in Scotland and will focus only on outcomes that can be identified using routine administrative data systems.

**Methods:**

This study is a natural experiment with a case-cohort design using linked anonymised routine health, educational and social care data. Cases will be women enrolled as FNP Clients in ten NHS Health Boards in Scotland and Controls will be women who met FNP eligibility criteria but were pregnant at a time when the programme was not recruiting. Outcomes are mapped to the Scottish FNP logic model. All comparative analyses will be pre-specified, conducted on an intention to treat basis and will use multilevel regression models to compare outcomes between groups.

**Discussion:**

The study protocol is based upon the specification of FNP commissioned by the Scottish Government. This study design is novel for the evaluation of the FNP/NFP programmes which are primarily evaluated with an RCT. Outcomes included within the study have been selected on the basis that they are outcomes FNP aims to influence and where there is routine data available to assess the outcome

## Introduction

### The importance of early life experiences for child health and development

Individual, social and economic circumstances faced by young mothers (19 years or under) can challenge a successful start in life for their children. Children born to young mothers have lower birth weights, are less likely to receive breast milk, have higher mortality rates, are more likely to suffer accidents, experience lower educational attainment, more emotional and behavioural problems, and become young parents themselves [1–4]. Young and economically disadvantaged mothers are also more likely to smoke thus increasing the risk of adverse health outcomes for themselves and their children [5]. 

### Intervening to support families

Intervening early in the lives of families with young mothers might enhance life chances for both mother and child. The Nurse Family Partnership (NFP) is an intensive preventative home-visiting service which involves up to 64 structured home visits across pregnancy, infancy and toddlerhood by specially recruited and trained family nurses from early pregnancy until children are 2 years of age. It is one of 12 programmes meeting Home Visiting Evidence of Effectiveness (HomVEE) criteria for an evidence based intervention [6]. Developed in the US with young first-time mothers, the programme aims to address the problems of poor birth outcomes, child abuse and neglect, and the diminished economic self-sufficiency of mothers [7]. The NFP draws upon theories of human ecology, self-efficacy and human attachment [8–10]. In three US trials, the NFP has demonstrated improvements in prenatal health behaviours and birth outcomes, improvements in sensitive care giving, reductions in child injuries, abuse and neglect, improvements in maternal life course (e.g. greater workforce participation, fewer subsequent pregnancies, and reduction in welfare requirements) and improvements in child and adolescent functioning [9, 11–18].

### International replication of NFP

A phased process of programme replication (adaptation to local context, pilot testing for feasibility and acceptability, randomised controlled trial (RCT), replication and expansion) underpins the adoption of the NFP in non-US settings. In England, the Family Nurse Partnership (FNP) programme was introduced in April 2007 across 10 pilot sites and was evaluated in the Building Blocks RCT (BB:0-2) at 18 sites which reported in October 2015 [19, 20]. The primary outcomes measured (as selected on the basis of three US trials and government priorities) were smoking in late pregnancy, birthweight, child admissions to hospital including A&E attendance before their second birthday and subsequent pregnancies within 24 months of the mother’s first child being born. The trial also looked at a range of secondary outcomes, including child development up to age two. The researchers found that adding FNP to the health and social care provided in England had no additional benefit on the primary outcomes while between-group differences were found for some secondary outcomes (including intention-to-breastfeed, maternally reported child cognitive development, language development). In a Dutch trial of NFP (the VoorZorg trial) where teenage pregnancy rates are much lower than in the UK, the intervention was offered following a two-stage selection process identifying women with multiple risk factors (e.g. psychological, health, economic, social). VoorZorg found NFP lowered rates of smoking in late pregnancy, and increased rates of breast feeding at six months post-birth [21, 22]. 

### FNP in Scotland

FNP was first introduced to Edinburgh Community Health Partnership (CHP) NHS Lothian in 2010 and was subject to an independent evaluation in 2013 focussing on its implementation in a Scottish context [23]. The evaluation concluded that it was possible to implement FNP with fidelity in Scotland and could plausibly deliver improved outcomes in pregnancy, child health and development, maternal health, and self-efficacy. The Scottish Government aimed to build on and supplement the existing national and international evidence base for FNP, and assess effectiveness and opportunities for optimisation of the programme, to guide decision making on maternal and child health in Scotland. Part of the licencing agreement for FNP stipulates that an RCT should be undertaken. In 2015, an independent evaluability assessment for FNP in Scotland was undertaken to identify options for carrying out an RCT style evaluation. The outcome of the evaluability assessment was that a natural experimental study using retrospective routinely collected data be undertaken as the preferred method for evaluating impact [24].

## Methods

### Study aim

This study will use anonymised individual level routinely collected data to evaluate the effectiveness of FNP in Scotland. The aim of this study is to examine the association between the provision of FNP, when added to existing services, and a range of outcomes covering maternal and child health, child development, and parental life course compared to existing services alone for first time teenage mothers.

### Study design

Following the Medical Research Council’s (MRC) guidance on natural experiments, the FNP Programme in Scotland will be evaluated using a case-cohort design [25]. A linked anonymised research database will be generated to compare routinely available health, education, and social care data between mothers to be in receipt of FNP (Cases) and a Control sample who would meet the criteria for FNP but not in receipt of support (Controls). 

### Study population

The population will be all women eligible for the FNP Programme from 1st January 2009 to 31st March 2016 and their first-born child(ren). 

### Identifying Cases and Controls

#### Cases

Cases will be women and first-borns enrolled as FNP Clients in the ten participating Scottish Health Boards (HB) since its initiation from 1st January 2010 to 31st March 2016. Eligible women (criteria in Table 1A) are usually referred to the local FNP team after their antenatal booking appointment at around 12 weeks gestation and are required to be enrolled in the programme before 29 weeks. Cases will be identified from the FNP Scottish Information System (FNP SIS).

**Table 1: Maternal baseline characteristics measured at (or before) date of antenatal booking/enrolment table-1:** ^1^Either Health Board level or smaller geographical area such as Community Health Partnership level or where a recruitment area was defined by travel time ^2^Derived by Electronic Data Research and Innovation Service (eDRIS) SMR: Scottish Morbidity Record

A. FNP Clients eligibility criteria	B. Eligibility criteria applied to fields within SMR 02 dataset to identify Controls
1. Living in an FNP-recruiting NHS Health Board	Postcode at antenatal booking mapped onto each FNP recruiting area1
2. First time mothers-to-be (women are eligible if a previous pregnancy resulted in a miscarriage, stillbirth or termination)	No previous live birth
3. Aged 19 years or younger at time of last menstrual period (LMP)	Derived variable2 based on date of birth and date of LMP
4. Less than 28+6 weeks gestation at enrolment into FNP	Gestation at booking date (derived variable2 based on date of booking and date of LMP)

Exclusion criteria

5. Mother-to-be will relinquish baby at birth	Not measurable at recruitment – minimal risk to numbers
6. Moving outside of the FNP catchment area before programme end	Not measurable at recruitment – minimal risk

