#### Controls

The FNP eligibility criteria in Table 1A will be applied to fields in the Scottish Morbidity Record (SMR) 02 Maternity Inpatients and Day Cases dataset to identify potential Controls for each of the areas within the ten participating HBs. Controls’ antenatal booking date will be taken as a proxy for FNP enrolment date (index date). Controls will be women that would have been potentially eligible for FNP, but whose antenatal booking occurred during a period when local FNP teams were not enrolling women. Alongside the eligibility criteria, using the start and end dates of FNP enrolment (including any intervals when cohorts ceased enrolment) provided to us by the FNP SIS, eDRIS will identify individual Controls with antenatal booking dates:

i. in the 12 months prior to initiation of FNP enrolment (Pre-FNP);

ii. in the 12 months post FNP enrolment (Post-FNP);

iii. between periods of FNP enrolment (i.e. when enrolment was temporarily suspended due to caseload capacity, usually up to a maximum concurrent caseload of 25 women, being reached) (Interval).

Further ineligibility criteria are applied to women during the FNP enrolment process, such as planning to place the child for adoption or moving out of the area, but cannot be applied in the selection of Controls as they are not assessed in the SMR02 (or any other dataset) at date of booking.

Within the enrolment period, a second cohort of women exist consisting of women eligible for enrolment into the programme during a period of active FNP enrolment and who:

iv. were approached for FNP but not enrolled to the programme;

v. were not approached (e.g. insufficient capacity in team to offer to all eligible women; near end of enrolment period and caseloads nearly full).

Following advice from the Public Benefit and Privacy Panel (PBPP), it was not possible to access individual level data for these women (in iv and v). However, it is important to note that these groups may have different demographic, social or personal characteristics from those that enrolled in the programme and may differ non-randomly from the Cases for some variables. As it would be beneficial to the evaluation to understand the characteristics of (iv) and (v) above and understand if they differ from Cases and Controls in anyway, aggregate statistics will be provided by eDRIS to the study team. 

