### Identification of Cases and Controls

#### Cases

The number of Cases identified and received from FNP SIS and matched to the SMR02 dataset by eDRIS will be reported. Additional checks will be made on the eligibility of FNP clients using SMR02 fields (age at enrolment vs age at booking, age at Last Menstrual Period gestational age at enrolment vs. booking). This will allow us to measure the robustness of these fields used to identify the Controls.

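### The gestation limit is applied at FNP enrolment for Cases but at antenatal booking for Controls, so late bookers may be over-represented among Controls, with a probably small bias of unknown direction

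*Protocol article*

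**What the plan says.** Table 1, under Identifying Cases and Controls, sets the FNP criteria beside the SMR02 fields used to find Controls. In row 4 the FNP criterion is "Less than 28+6 weeks gestation at enrolment into FNP", and the Control field is "Gestation at booking date (derived variable2 based on date of booking and date of LMP".

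The Cases section gives the order of events. Eligible women "are usually referred to the local FNP team after their antenatal booking appointment at around 12 weeks gestation and are required to be enrolled" before 29 weeks. Booking comes first, referral second and enrolment third.

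The Controls section says "The FNP eligibility criteria in Table 1A will be applied to fields in the Scottish Morbidity Record (SMR) 02 Maternity Inpatients and Day Cases dataset", and states the substitution openly: "Controls’ antenatal booking date will be taken as a proxy for FNP enrolment date (index date".

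Four later statements bear on the point:
- Identification of Cases and Controls (Analysis), Cases: a check in Cases will compare "gestational age at enrolment vs. booking", to judge how robust the fields used to find Controls are.
- The same section, Controls: all Controls are kept. Further matching is rejected because it could lose Cases and sample size.
- Main analyses: adjustment for imbalance in confounders is listed as a sensitivity analysis.
- The covariate table under Descriptive analysis: gestation is a single row whose label joins booking date and FNP enrolment date, sourced to SMR02 and FNP SIS.

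**The concern.** One numerical limit is used at two different points in the pathway. A Case must have booked, been referred and been enrolled before it. A Control need only have booked before it. A woman who books near the limit is therefore certain to enter the Control group in a Control window, but may well not become a Case in an enrolment window. The two groups then have different distributions of gestation at booking, and near the limit they hardly overlap.

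This concerns who enters each group. It would remain even if follow-up started at the same moment in both. It sits in the cohort definition, so it touches all 34 formally analysed outcomes, and a larger sample does not shrink it. If late bookers differ in prognosis, part of any difference between Cases and Controls would reflect when women booked and not FNP.

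**Working it through.** There is no stated figure to reproduce: the article gives no booking-to-enrolment lag, no spread of booking gestation and no outcome risk for late bookers. Step 1 uses the document alone. Steps 2 to 4 rest on assumptions.

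**1. Time left after booking.** The limit is 28 × 7 + 6 = 202 days. Days left = 202 − 7 × booking week.

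| Booking week | Days to 28+6 |
|---|---|
| 12 | 118 |
| 20 | 62 |
| 24 | 34 |
| 26 | 20 |
| 28 | 6 |

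At the usual booking time there is ample room. The mismatch affects only women who book late.

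**2. How many women (assumed).** Take mean booking gestation of 12.5–13 weeks, SD 4.5–5.5 (gamma, shifted to start at 6 weeks), and a mean lag of 4–6 weeks (gamma). Require booking plus lag below 28+6 for Cases, and booking alone below 28+6 for Controls.
- Booking at 22 weeks or later: 3.5–5.4% of Controls against about 2% of Cases.
- Booking at 24 weeks or later: 1.8–3.0% against about 0.5–0.7%.

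The excess at 22 weeks or later is 3.5 − 2 = 1.5 to 5.4 − 2 = 3.4 percentage points. A re-run with varied settings gave similar shares.

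**3. Size of a spurious difference if late bookers are at higher risk (assumed).** With no FNP effect, bias ≈ excess share × risk gap. The standard error uses the roughly 3000 Cases and 6000 Controls under Power calculation: SE = √[p(1−p)(1/3000 + 1/6000)].
- 12–14% against 7%: 0.015 × 5 = 0.08 points to 0.034 × 7 = 0.24 points. SE at p = 0.07 is 0.57 points.
- 40–45% against 30%: 0.015 × 10 = 0.15 points to 0.034 × 15 = 0.51 points. SE at p = 0.30 is 1.02 points.

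The full simulation gives 0.07–0.25 and 0.14–0.53 points. Either way this is about 0.1 to 0.5 standard errors.

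**4. Wider range, either direction (assumed).** Let s be the excess share, r the relative risk in late bookers and p the base risk. Control risk = p(1−s) + r·p·s. The spurious odds ratio is the odds at p divided by the odds at the Control risk.

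| p | s | r | Control risk | Spurious OR |
|---|---|---|---|---|
| 0.10 | 2% | 1.5 | 0.1010 | 0.989 |
| 0.10 | 5% | 1.5 | 0.1025 | 0.973 |
| 0.10 | 5% | 0.8 | 0.0990 | 1.011 |
| 0.10 | 10% | 2.0 | 0.1100 | 0.899 |
| 0.30 | 10% | 2.0 | 0.3300 | 0.870 |

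With 3000 against 6000, the 95% interval around a null odds ratio is about 0.86–1.16 at p = 0.10 and 0.91–1.10 at p = 0.30. Only the last row falls outside its interval. It needs a 10% excess, well above the 1 to 4 points in step 2.

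**5. What the planned safeguards do.** The check in Cases measures the lag, but no action on Controls follows from it. Keeping all Controls leaves the late bookers in. Adjustment as a sensitivity analysis leaves the main estimate as it is. The gestation covariate can be read as booking for Controls and enrolment for Cases. On that reading Cases would look later than Controls even with identical booking patterns, so both the balance table and any adjustment would compare different quantities.

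**The case against.** The strongest objection is to the direction. A reader might infer that the mismatch makes Controls higher risk and therefore always flatters FNP. The documents do not support that. Nowhere do they say that late bookers are at higher risk. Step 3 assumes the direction, so it cannot be evidence for it, and step 4 shows the sign reversing when r is below 1. A woman who books near 28 weeks is still pregnant at that point, so she cannot contribute an earlier loss or a very early birth. The sign may thus differ by outcome. On selection into enrolment generally, the article itself says that the effect could be under- or overestimated. This objection stands.

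Second, the effect is small on its own assumptions, and all comparisons are declared exploratory. That also stands, and it limits the weight of the point.

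Third, the article is open about the proxy, plans a check of it, plans adjustment for imbalance, and concedes in the Discussion that women who would not have enrolled remain among Controls. This stands in part. The Discussion says such women cannot be identified for removal. Late bookers can be: booking date and LMP are in SMR02 for Controls, and Cases are matched to SMR02.

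Fourth, the covariate row does not say outright that a different time point is used in each group, and the analysis plan may settle it. This is right, so the row is ambiguous and not a demonstrated error.

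Fifth, the article deliberately keeps all Controls for generalisability and power. But what it weighs and rejects is matching that could exclude Cases, not restriction to booking gestations common to both groups, which should lose few women.

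**Conclusion.** The mismatch is in the text: one limit, applied at enrolment for Cases and at booking for Controls. Controls can therefore include women who booked too late to have been enrolled in practice, and none of the planned steps takes them out of the main comparison.

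The bias is probably small, about 0.1 to 0.5 standard errors under the assumed distributions and risks, and its direction is unknown. It would favour FNP if late bookers are at higher risk, which the documents do not state. A material bias would need a much larger excess of late bookers than those assumptions give. The article does not supply the figures that would settle the matter, but the linked data will. This is a cheap improvement worth making before outcomes are seen, not a defect that undermines the study.

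**What to change.** - Use SMR02 gestation at booking as the common gestation variable in both groups, for cohort definition, the balance table and any adjustment. If gestation at enrolment is also reported for Cases, give it a separate row.
- Before outcomes are seen, use the planned booking-versus-enrolment check to find the range of booking gestations in which Cases actually occur. Write that range into the analysis plan.
- Restrict both groups to that range in the main analysis, or at least in a pre-specified sensitivity analysis, and report how many women are dropped from each group.

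Adjusting for booking gestation in both groups would address the same imbalance without dropping anyone, but near the limit, where Cases are almost absent, it relies on extrapolation.

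The cost is a line in the cohort-definition code and a sentence in the analysis plan. Under the assumptions above, a few percent of Controls and very few Cases are lost. Results would no longer cover very late bookers.

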#### Controls

The FNP eligibility criteria in Table 1A will be applied to fields in the Scottish Morbidity Record (SMR) 02 Maternity Inpatients and Day Cases dataset to identify potential Controls for each of the areas within the ten participating HBs. Controls’ antenatal booking date will be taken as a proxy for FNP enrolment date (index date). Controls will be women that would have been potentially eligible for FNP, but whose antenatal booking occurred during a period when local FNP teams were not enrolling women. Alongside the eligibility criteria, using the start and end dates of FNP enrolment (including any intervals when cohorts ceased enrolment) provided to us by the FNP SIS, eDRIS will identify individual Controls with antenatal booking dates:

i. in the 12 months prior to initiation of FNP enrolment (Pre-FNP);

ii. in the 12 months post FNP enrolment (Post-FNP);

iii. between periods of FNP enrolment (i.e. when enrolment was temporarily suspended due to caseload capacity, usually up to a maximum concurrent caseload of 25 women, being reached) (Interval).

Further ineligibility criteria are applied to women during the FNP enrolment process, such as planning to place the child for adoption or moving out of the area, but cannot be applied in the selection of Controls as they are not assessed in the SMR02 (or any other dataset) at date of booking.

Within the enrolment period, a second cohort of women exist consisting of women eligible for enrolment into the programme during a period of active FNP enrolment and who:

iv. were approached for FNP but not enrolled to the programme;

v. were not approached (e.g. insufficient capacity in team to offer to all eligible women; near end of enrolment period and caseloads nearly full).

Following advice from the Public Benefit and Privacy Panel (PBPP), it was not possible to access individual level data for these women (in iv and v). However, it is important to note that these groups may have different demographic, social or personal characteristics from those that enrolled in the programme and may differ non-randomly from the Cases for some variables. As it would be beneficial to the evaluation to understand the characteristics of (iv) and (v) above and understand if they differ from Cases and Controls in anyway, aggregate statistics will be provided by eDRIS to the study team. 

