### Identifying children

A mother-child link is available within the SMR02 enabling a flag for children born after the FNP enrolment date (Cases) / antenatal booking date (Controls) to be derived. 

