## Analysis

### Power calculation

In this retrospective study, the sample size is fixed. The Evaluability Assessment estimated around 3000 births in FNP cohorts between 2010 and 2015 and around 6000 in the Controls [24]. This large sample size would permit very precise estimation of overall intervention effects for a primary or co-primary outcomes. However as specified by Scottish Government, there is no pre-specified prioritisation of the short- or medium-term outcomes and as such no power calculation is necessary. 

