### Main analyses

With no primary outcome, equal importance will be given to each short and medium term outcome. All comparative analyses will therefore be exploratory, pre-specified and conducted on an intention to treat (ITT) basis. ITT in this study means that the analysis will include everyone who started the programme, according to their original ‘allocation’, i.e. the intervention group will be women enrolled in FNP regardless of the treatment (intervention) they actually received.

All analyses will compare outcomes (intervention effect) between the two groups (Cases and Controls) using multilevel regression models, to allow for clustering of outcome within NHS HB, and FNP team/cohort (where more than one team runs within a HB). Multiple births will be analysed as separate children and the potential clustering of outcome will not be taken account for in analyses due to the small numbers expected. Intervention effects will also be examined over time and between different geographical areas (HB and team/cohort) by fitting multilevel models and interactions (group x year). Alongside the estimate of effect, for all outcomes a 95% confidence interval (CI) and unadjusted p-value will be presented.

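### Controls are indexed at booking and Cases at the later FNP enrolment, so pregnancies ending in between can be counted only among Controls

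*Protocol article*

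**What the plan says.** All references are to the protocol article.

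- **Cases.** The section describes eligible women as "usually referred to the local FNP team after their antenatal booking appointment at around 12 weeks gestation". The latest permitted enrolment is just short of week 29, and Table 1A puts the limit at less than 28+6 weeks. Under Main analyses, the intention-to-treat rule starts from enrolment: "the intervention group will be women enrolled in FNP regardless of the treatment".
- **Controls.** The Controls section states that "antenatal booking date will be taken as a proxy for FNP enrolment date (index date". Table 1B applies the gestation limit to "Gestation at booking date (derived variable2 based on date of booking and date of LMP", not to a time comparable with enrolment.
- **Children.** Under Identifying children, the mother-child link uses the same two anchors: "children born after the FNP enrolment date (Cases) / antenatal booking date (Controls) to be derived".
- **Covariates.** The baseline table under Descriptive analysis has a single gestation variable, taken at booking or at FNP enrolment. It lists pregnancy outcome (live birth, stillbirth, termination) as a baseline characteristic.
- **Checks.** In the Analysis section, Identification of Cases and Controls plans to compare gestation at enrolment with gestation at booking among Cases, but only to test eligibility and the reliability of the fields.
- **Limitations.** The Discussion deals with women who were not enrolled. It does not mention the interval between booking and enrolment.

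**The concern.** On the protocol's own account enrolment follows referral, and referral follows booking. Booking is therefore not a neutral stand-in for enrolment but a systematically earlier date. A woman whose pregnancy ends after booking and before enrolment never becomes a Case. The same woman booking in a non-enrolling period stays in the Control group. For events that end a pregnancy this is immortal time in the Case group, and a large sample does not reduce it.

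Two further effects follow. The Case birth cohort is selected on survival to enrolment, which slightly alters its composition relative to Controls. And any antenatal count that starts at the index date covers a longer stretch of pregnancy in Controls than in Cases.

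The article describes no landmark, delayed entry or matched index gestation. Adjusting for the gestation covariate would not help, because it measures a different time point in each group. Confounder adjustment is in any case planned only as a sensitivity analysis.

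**Working it through.** The protocol states no figure bearing on this point, so there is none to reproduce. The check reads the index rules side by side and then illustrates what they do when FNP has no effect.

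**Inputs from the protocol.** Booking at around 12 weeks; enrolment limit 28+6 weeks; group sizes of "around 3000 births in FNP cohorts between 2010 and 2015 and around 6000 in the Controls" (Power calculation), used here as approximate numbers of pregnancies.

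**Assumed inputs, because the protocol gives none.** Enrolment week g, taken as the same for all Cases; event rates; even spread of events over time.

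**Length of the gap.** 28+6 weeks is 28.86; 28.86 − 12 = 16.86, so up to about 16.9 weeks.

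**(a) Pregnancy loss.** Assume a risk L of 1% to 4%, spread evenly over weeks 12 to 24. Cases escape the share before enrolment, L(g − 12)/12. Their remaining risk is p = [L − L(g − 12)/12] / [1 − L(g − 12)/12]. The odds ratio against Controls then reduces to (24 − g)/12, whatever L is. The last column is the chance of a two-sided 5% significant result favouring FNP, by a two-proportion approximation at 3000 against 6000, as L runs from 1% to 4%.

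| Enrolment week | Odds ratio under no effect | Chance of a false significant result |
|---|---|---|
| 14 | 10/12 = 0.83 | 11% to 32% |
| 16 | 8/12 = 0.67 | 34% to 89% |
| 18 | 6/12 = 0.50 | 71% to nearly 100% |

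Example: L = 2%, g = 16. Cases escape 0.02 × 4/12 = 0.0067, so p = 0.0133/0.9933 = 0.0134 against 0.02 in Controls; the odds ratio is 0.67 and the chance of a false significant result is 61%.

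**(b) Preterm birth before 37 weeks.** Assume that a share f of 5% to 12% of preterm births fall evenly over weeks 24 to 29. The odds ratio is 1 − f(g − 24)/5 for g from 24 up.

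- Enrolment by week 24: 1.00.
- Week 26: 1 − 0.05 × 2/5 = 0.98 to 1 − 0.12 × 2/5 = 0.95.
- All Cases at the 28+6 limit: 1 − 0.05 × 4.86/5 = 0.95 to 1 − 0.12 × 4.86/5 = 0.88.

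**(c) Antenatal counts from the index date to week 40.** With a constant rate and no exposure offset, the rate ratio is (40 − g)/(40 − 12): 26/28 = 0.93 at week 14, 24/28 = 0.86 at week 16 and 22/28 = 0.79 at week 18. A correct person-time offset brings it back to 1.

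**After alignment.** With one time zero, or with Controls required to be still pregnant at a matched gestation, the expected ratio under no effect is 1.0 in these illustrations.

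**The case against.** The outcome list is not in the text available. Data sources and outcomes says only that the short-term outcomes are likely to relate to pregnancy, birth and the time up to the second birthday. Pregnancy loss is not named as an outcome, and pregnancy outcome appears among the baseline variables. The largest illustrated bias may therefore attach to something that is never tested. This stands, and it makes the conclusion conditional.

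A reader might infer that Cases can have no event at all between booking and enrolment. That is true only of events that end the pregnancy. Cases can be admitted, attend or receive prescriptions in the gap. Whether these are counted depends on outcome windows that may be set in the separate statistical analysis plan. Counts are to be reported as incidence rate ratios, which usually rest on person-time, and the article does not say whether an offset will be used.

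A reader might also infer that preterm birth in general is biased, or that every distortion favours FNP. Neither is supported. Part (b) shows almost no effect on preterm birth unless enrolment is late. A shorter window lowers beneficial contacts as well as adverse events. Child and school outcomes timed from birth have equal follow-up.

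Finally, all comparisons are declared exploratory. That bears on how the results are read, but it does not remove a bias built into the cohort definition. Nor is the index date a detail left to a later plan: the article states it, and the Control cohort is extracted by it.

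**Conclusion.** The point holds in limited form. The two groups have different time zeros, Cases are selected on a pregnancy still continuing at enrolment, and nothing in the article corrects this. For loss, termination or births before about 29 weeks, the comparison favours FNP wherever such an outcome is analysed. Antenatal counts taken from the index date are distorted, in a direction that depends on the outcome, unless the window or the exposure time is made equal. Preterm birth under 37 weeks is little affected unless many Cases enrol after 24 weeks. Outcomes timed from birth are touched only through the composition of the birth cohort.

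The mechanism follows from the text. The size does not, because the protocol gives neither the distribution of enrolment gestation nor the event rates. The odds ratios and rate ratios above show what the rule could produce under assumed inputs and are not estimates for this study.

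**What to change.** For pregnancy and birth outcomes, use one of two routes.

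1. **Matched index gestation.** Give each Control an index gestation drawn from the enrolment gestations of Cases in the same Health Board. Limit the draw to values at or after that Control's own booking gestation; otherwise a late-booking Control would acquire immortal time of her own. Keep only Controls still pregnant at the drawn gestation. Control status stays defined by booking date, so a later index falling in an enrolling period does not reclassify anyone.
2. **Common origin.** Use SMR02 booking as the origin in both groups, with delayed entry of Cases at enrolment. This needs a time-to-event model, since a plain logistic model cannot take late entry.

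With either route:

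- count antenatal events over the same window in both groups, or with a person-time offset;
- take baseline covariates from the SMR02 booking record in both groups;
- keep gestation at booking and gestation at enrolment as separate variables;
- report a landmark analysis of pregnancies continuing at 29+0 weeks only as a sensitivity analysis, because it conditions on survival after enrolment and could remove a real effect.

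The dates needed are already in SMR02 and FNP SIS. The cost is derivation work, revised wording and, under the first route, a small number of Controls. With losses as assumed in (a) and a drawn gestation of 16 weeks, that is 6000 × 0.01 × 4/12 = 20 to 6000 × 0.04 × 4/12 = 80 Controls.
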